| Discontinuation criteria for each subject | The study will be discontinued for the subject who meets any of the following criteria.   1. The subject himself offered to withdraw from the study participation 2. The subject who could not comply with the prescribed administration of diclofenac sodium and study drug 3. The subject for whom the prescribed test was not performed 4. The subject who was judged impossible to move to the study period by the investigator, etc. 5. The subject who turned out that he did not meet the inclusion criteria or violated the exclusion criteria after the start of the study 6. The subject for whom the investigator, etc. judged that the study should be discontinued |
| Endpoints | [Efficacy endpoints]  Primary endpoint: Permeability of the small intestine using the lactulose/mannitol test  Secondary endpoints: endotoxin activity in blood, changes in intestinal flora  [Safety endpoints]  Adverse events, adverse reactions |
| Scheduled study period | May 2015 - March 2016 |

1. Background of this study

The results of the basic experiments suggest the correlation between small-intestinal mucosal injury and increase in the intestinal permeability and also the relationship with another disease recognized as Leaky Gut Syndrome.

Lubiprostone (brand name: Amitiza^®^ Capsules 24 µg (hereinafter referred to as the study drug) is a drug approved in November 2012 with “chronic constipation” as an indication. Since it is a prostaglandin derivative, it is reported from the basic experiments that the drug may prevent the onset of small-intestinal mucosal injury and increase in the intestinal permeability.

In this study, the effect of this study drug to contribute to the suppression of intestinal permeability will be examined by comparing the subjects in the study drug treatment group with those in the non-treatment group.

1. Objectives
   1. Primary objective

To evaluate permeability of the small intestine using the lactulose/mannitol test.

- 1. Secondary objectives

To evaluate endotoxin activity in blood.

To evaluate changes in the intestinal flora.

1. Subjects

The healthy adults who meet all of the following “3.1 Inclusion criteria” and do not correspond to any of the following “3.2 Exclusion criteria” will be the subjects in this study.

- 1. Inclusion criteria
     - 1. Men at age ≥20 years but <60 years when the consent was obtained

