- - - 1. Administer diclofenac sodium (75 mg/day) three times a day after every meal for 7 days.
      2. After administering diclofenac sodium for 7 days, the investigator, etc. will perform medical examination and allocate the subjects who can move to the study period to either a study drug treatment group or a control group.
      3. The lactulose/mannitol test, measurement of endotoxin activity in blood, and intestinal flora test will be performed.

For the first 6 subjects (3 subjects in each group) after the start of the study, the study treatment period or non-treatment period will be 28 days. For the 7th subject and after that, the study treatment period or non-treatment period will be determined to be either 14 days or 28 days based on the results of the 6 subjects.

[Up to the first 6 subjects]

[Study period]

(In the case of the study treatment group)

- - - 1. Administer 1 capsule of the study drug once a day after lunch for 14 days. The subjects are instructed to comply with the “Rules to be followed by subjects”.
      2. After administering the study drug for 14 days, the investigator, etc. will perform medical examination, as well as lactulose/mannitol test, measurement of endotoxin activity in blood, and intestinal flora test.
      3. Administer 1 capsule of the study drug once a day after lunch for 14 days.
      4. After administering the study drug for 14 days, the investigator, etc. will perform medical examination, as well as lactulose/mannitol test, measurement of endotoxin activity in blood, and intestinal flora test.

(In the case of the control group)

- - - 1. The study drug will not be administered (for 14 days). The subjects are instructed to comply with the “Rules to be followed by subjects”.
      2. After 14 days, the investigator, etc. will perform medical examination, as well as lactulose/mannitol test, measurement of endotoxin activity in blood, and intestinal flora test.
      3. The study drug will not be administered (for 14 days).
      4. After 14 days, the investigator, etc. will perform medical examination, as well as lactulose/mannitol test, measurement of endotoxin activity in blood, and intestinal flora test.

[After the 7th subject]

[Study period]

(In the case of the study treatment group)

- - - 1. Administer 1 capsule of the study drug once a day after lunch for 14 days or 28 days. The subjects are instructed to comply with the “Rules to be followed by subjects”.

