- - - 1. Subjects take diclofenac sodium and study drug according to the instructions given by the investigator, etc.
      2. If a subject missed (could not) to take study drug after lunch, he/she takes it after supper. If he/she missed (could not) to take study drug after supper, he/she takes no study drug on that day.
      3. During the study period, combined treatments [medications (including supplements) and therapies] are prohibited, unless the investigator, etc. considers that use of combined treatment is necessary for treating adverse event(s) that occurred in a subject(s) during the course of the study.
      4. If a subject experienced any abnormality during the study period, he/she must inform the investigator, etc. of it.
      5. Any subject must not drink a large of alcohol during the study period.
      6. It is not allowed to take any food or drink from 21:00 onward on the day before and the day when lactulose/mannitol test is performed. However, a small amount of drink without sugar content is allowed.

1. Items and time points for investigations/examinations
   1. Patient characteristics

Investigation items: date of birth, gender, height, weight, complication, past medical history, history of allergy, concomitant drug, frequency of bowel movement, stool condition, with or without use of purgative

Target groups: study drug group, control group

Time points of investigation: Screening period

- 1. Vital signs

Investigation items: blood pressure, pulse rate

Target groups: study drug group, control group

Time points of investigation: screening period, at the time when an adverse event occurred, at the time of discontinuation

- 1. Physical findings

Investigation items: subjective or objective findings, adverse events, nausea, frequency of bowel movement, stool conditions

Target groups: study drug group, control group
Time points of investigation: screening period, period for treatment with diclofenac, period for treatment with study drug, at the time of discontinuation

- 1. Compliance to diclofenac

Investigation items: treatment period, daily dose, cessation/discontinuation of medication, reason of cessation/discontinuation of medication, reason for change

Target groups: study drug group, control group

Time points of investigation: Period for treatment with diclofenac

- 1. Compliance to study drug

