Investigation items: treatment period, daily dose, cessation/discontinuation of medication, reason of cessation/discontinuation of medication, reason for change

Target groups: Study drug treatment group

Time points of investigation: Period for treatment with study drug

- 1. Lactulose/mannitol test

Target groups: study drug group, control group

Time points of investigation: screening period, period for treatment with diclofenac, period for treatment with study drug, at the time of discontinuation

- 1. Endotoxin activity in blood

Target groups: study drug group, control group

Time points of investigation: screening period, period for treatment with diclofenac, period for treatment with study drug, at the time of discontinuation

Volume of blood to be collected: 2 mL in each time

- 1. Intestinal flora

Target groups: study drug group, control group

Time points of investigation: screening period, period for treatment with diclofenac, period for treatment with study drug, at the time of discontinuation

1. Endpoints
   1. Efficacy endpoints

Primary endpoint: Permeability of the small intestine using the lactulose/mannitol test

Secondary endpoints: endotoxin activity in blood, changes in intestinal flora

- 1. Safety endpoints

Adverse events, adverse reactions

1. Adverse events
   1. Adverse events

An adverse event is defined as any untoward medical occurrence (including abnormal laboratory findings) in a subject and which does not necessarily have to have a causal relationship with study drug. In this study, adverse events will be collected during the period from the start of treatment with diclofenac sodium to the end of treatment with study drug.

Adverse events will be assessed based on the clinical symptoms observed in subjects.

All adverse events will be documented by the investigator, etc. on the case report form to record the dates of its occurrence and resolution, its seriousness and severity, whether the subject was treated or not, its outcomes and the results of evaluation of causal relationship between the event and study drug.

- 1. Serious adverse events

A serious adverse event includes those described below.

- - - 1. Death
      2. Any adverse event which may lead to death
      3. Any adverse event which requires admission to a hospital or clinic, or prolongation of existing hospitalization (excluding hospitalization for routine tests)
      4. Disability
      5. Any adverse event which may result in disability

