An unexpected adverse reaction is that which is not listed in the Interview Form of study drug (2014) or that which is listed in the Interview Form but its nature or severity is different from that described in the Interview Form.

- 1. Expected adverse reactions of study drug

Expected adverse reactions of Voltaren include the following events [based on the Interview Form of study drug (2015)].

Among the 1,474 subjects investigated until the approval, 239 adverse reactions were observed in 160 subjects (10.85%). Gastrointestinal symptoms such as gastric distress occurred in 139 subjects (9.43%) as major symptoms. Other symptoms included edema observed in 14 subjects (0.95%) and skin symptoms such as rash in 23 subjects (1.56%).

In the post-marketing drug-use result survey, 4,545 adverse reactions were observed in 2,749 (7.71%) out of the 35,653 subjects. As symptoms, gastrointestinal symptoms were observed in 2,365 subjects (6.63%) followed by general symptoms such as edema in 215 subjects (0.60%) and skin symptoms in 172 subjects (0.48%).

Reports of gastric ulcer and liver disorder as other adverse reactions accounted for below 0.1%.

Expected adverse reactions of Amitiza include the following events [based on the Interview Form of study drug (2014)].

Adverse reactions including abnormal laboratory findings were found in 196 (62%) /315 subjects who received study drug at a dose of 48 μg/day (24 μg b.i.d.) in 3 Japanese clinical studies. Most commonly observed adverse reactions included diarrhea in 95 subjects (30%) and nausea in 73 subjects (23%).

1. Study termination criteria in subjects

The study will be discontinued for the subject who meets any of the following criteria.

- - - 1. The subject himself offered to withdraw from the study participation
      2. The subject who could not comply with the prescribed administration of diclofenac sodium and study drug
      3. The subject for whom the prescribed test was not performed
      4. The subject who was judged impossible to move to the study period by the investigator, etc.
      5. The subject who turned out that he did not meet the inclusion criteria or violated the exclusion criteria after the start of the study
      6. The subject who developed an adverse reaction that falls under the category of Grade 2 or higher adverse reaction according to CTCAC v4.0 (moderate or severe prescribed in Section 11.6)

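### Adverse-event collection is tied to the end of lubiprostone treatment: it closes early for treated subjects who stop early, names no end for controls, and leaves open events without a follow-up rule

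*Protocol*

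**What the plan says.** The collection window is set in one sentence of Protocol Section 11.1 (Adverse events): "adverse events will be collected during the period from the start of treatment with diclofenac sodium to the end of treatment with study drug". Section 1 (Background) fixes the term by introducing lubiprostone as "hereinafter referred to as the study drug) is a drug approved in November 2012".

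The periods that this window spans are in Section 8.2 (Study procedures):

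- Everyone first takes diclofenac: "Administer diclofenac sodium (75 mg/day) three times a day after every meal for 7 days". Allocation follows.
- From the 7th subject on, the treated group's instruction is: "Administer 1 capsule of the study drug once a day after lunch for 14 days or 28 days". The first six subjects have 28 days, with a visit at day 14.
- Controls take none over the same 14 or 28 days.

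Section 9.3 (Physical findings) includes adverse events among its items, names both groups as targets, and gives "Time points of investigation: screening period, period for treatment with diclofenac, period for treatment with study drug, at the time of discontinuation".

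Section 12 (Study termination criteria in subjects) takes out of the study, among others, "The subject who developed an adverse reaction that falls under the category of Grade 2 or higher adverse reaction". It closes by saying that tests after discontinuation are as a rule not done unless the subject asks for them.

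Section 11.1 also requires the case report form, for every event, "to record the dates of its occurrence and resolution, its seriousness and severity, whether the subject was treated or not, its outcomes". Section 22.4 (Analysis methods for safety endpoints) compares type, severity and incidence between the two groups.

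**The concern.** The end of the window is a dosing event, not a study day. For a treated subject, stopping lubiprostone and ending adverse-event collection are the same moment, so harm that stops treatment also stops observation. For a control the sentence points to an event that never happens.

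Adverse events and reactions are the trial's only safety endpoints, and they are to be compared between groups. If observation time depends on treatment in one arm and is unstated in the other, the incidences do not rest on the same time at risk. Later or second events would be missed mainly in treated subjects stopped early, which would tend to make lubiprostone look better than it is.

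The outcome of an event is also least likely to be known where it matters most: in an event that ended participation, or in one still present at the last dose. These are healthy volunteers in whom raised gut permeability is induced on purpose.

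**Working it through.** The plan states no figure on this point. The check sets the sections side by side and counts days.

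**1. Who is covered, and until when**

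| Subject | End under the Section 11.1 sentence | What other sections add |
|---|---|---|
| Lubiprostone, completes | Last dose, day 14 or 28 | Sections 9.6 to 9.8 place the closing tests in the study-drug period, and Section 9.3 places an adverse-event check in that same period |
| Lubiprostone, stopped early | Day of stopping | Section 9.3: one check at discontinuation; nothing after it |
| Control | None named | Section 9.3 names the control group; the Section 8.3 schedule uses the study-drug period for controls with a no-administration row, and its footnote equates the treatment and non-treatment periods |
| Took diclofenac, not allocated | None named | Meets a Section 12 criterion, so the discontinuation check applies; nothing after it |

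**2. Why early closure falls mainly on one arm**

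The part of Section 11 that defines adverse reactions ties them to a causal relation with study drug. After allocation, the Grade 2 criterion in Section 12 therefore applies mainly to lubiprostone subjects.

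**3. Observation time**

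Inputs: diclofenac period 7 days; planned study period T = 14 or 28 days; d = study-drug day of stopping. The documents give no value of d. Days 3 and 7 are assumptions for illustration.

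Planned window = 7 + T, which is 7 + 14 = 21 or 7 + 28 = 35 days.

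Window for a treated subject stopped on day d = 7 + d. Share of plan = (7 + d)/(7 + T).

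| d (assumed) | Days collected | Share if T = 14 | Share if T = 28 |
|---|---|---|---|
| 3 | 7 + 3 = 10 | 10/21 = 48% | 10/35 = 29% |
| 7 | 7 + 7 = 14 | 14/21 = 67% | 14/35 = 40% |

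A control followed over the period implied by Sections 8.3 and 9.3 contributes the full 21 or 35 days.

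**4. Open events**

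The form asks for resolution date and outcome for all events. No section states who follows an event that is still open at the last dose, at discontinuation or at non-allocation, or for how long.

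**5. After the change**

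With one calendar window, every subject has a planned 21 or 35 days, whatever his group and whether or not treatment stopped early.

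**The case against.** Much of the protocol limits the damage.

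- **Controls are not left unobserved.** Sections 8.3 and 9.3 apply the study-drug period and its adverse-event check to them. This stands: for controls the defect is a loose sentence, not missing collection. A reader might infer that their window closes with diclofenac after 7 days, since diclofenac is listed under the Study drugs heading. The documents do not support that. Section 11.1 names diclofenac as the start and study drug as the end, Section 1 defines study drug as lubiprostone, and Section 9.3 carries the checks on.
- **The final visit is not outside the window.** A reader might infer this because the visit follows the last dose. The protocol files the closing tests under the study-drug period, so it treats that visit as part of it.
- **The form's requirement is not contradicted.** The window limits which events are collected. It does not forbid a later resolution date or an outcome of not resolved. What is missing is the follow-up rule.
- **Care is not absent.** The part of Section 11 on reporting and handling obliges the investigator to act medically on any event he learns of, and Section 13 obliges the site to treat research-related injury. Neither requires an event to be followed until it resolves.
- **The bias is limited.** A subject stopped for a reaction already counts as having had an event; only later, different events and outcomes are lost. A control who discontinues also has his last check then. This is a pilot of 30 or 35 subjects (Sections 22.5 and 6 differ), and Section 22.4 names no test.

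What survives is early closure on stopping, an unstated end for controls, and no rule for open events.

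**Conclusion.** The point holds in this form: followed exactly, the Section 11.1 sentence loses later events and outcomes mainly in treated subjects stopped early, and it gives controls no end point of its own. Stopping on day 3 would leave 48% or 29% of the planned window, and stopping on day 7 would leave 67% or 40%. These shares rest on assumed stopping days and on reading study drug as lubiprostone; the documents do not say how many subjects will stop or when.

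A reader might also be tempted to use the diarrhoea (30%) and nausea (23%) rates quoted in Section 11 to predict that several subjects will have an event open at the last dose. The documents do not support that. Those rates come from 48 µg/day, whereas this trial gives one 24 µg capsule daily, and they describe how often events occur, not how long they last.

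The effect is on the safety comparison and the completeness of event outcomes. It should be corrected, because the correction is small.

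**What to change.** In Section 11.1, replace the end of the window with a calendar end common to both groups: from the start of diclofenac through the scheduled day-14 or day-28 visit, that visit included, whether or not the subject is still on treatment, unless he declines further contact.

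Add that any event open at that visit, at discontinuation or at non-allocation is followed by the investigator, by telephone if need be, until its resolution date or final outcome is entered on the case report form.

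Reconcile the Section 8.3 schedule, the discontinuation time points in Section 9, Section 11.1 and the closing sentence of Section 12, so that the rule on tests after discontinuation is not read as ending adverse-event collection.

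The change touches no dose, stopping criterion or test. It costs a few sentences of protocol text, which as an amendment need ethics committee approval under Section 15, and a few telephone contacts. Some additional events will be reported.

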      6. Any adverse event which is serious pursuant to 1)-5)
      7. Any congenital disease or anomaly in later generations.
  1. Reporting and handling of adverse events

When the investigator, etc. learned occurrence of any adverse event in a subject, he or she would take adequate medical actions to ensure safety of the subject, above everything else, within the treatment covered by health insurance (e.g., endoscopic examination, treatment with medication). In addition, the investigator, etc. will inform MR of Abbott Japan Co., Ltd. who is in charge of the study site on all the adverse events (serious and non-serious) caused by lubiprostone, immediately after those events occurred. Furthermore, if any serious adverse event occurred during the course of this study, the investigator, etc. will inform the head of the study site also on the event.

- 1. Causal relationship between an adverse event and study drug

Assessment results of causal relationship between an adverse event and study drug would be classified as follows:

- - - 1. Related
         Temporal relationship is observed clearly and causes other than study drug can be excluded
      2. Unrelated
         No temporal relationship is observed or the event can be explained by other causes.
  1. Intensity (severity) of adverse event

The intensity of the adverse event would be judged based on the following:

- - - 1. Mild
         The adverse event causes no interference with usual activities of the subject. He does not require treatment for any condition.
      2. Moderate
         The adverse event causes some interference with usual activities of the subject. Treatment for symptoms associated with the event or premature discontinuation of the study (except for premature discontinuation due to his request) is required.
      3. Severe
         The adverse event causes inability to perform usual activities of the subject. Premature discontinuation of the study (except for premature discontinuation due to his request) and treatment of the subject are required.
  1. Definitions of adverse reactions

When causal relationship between an adverse event and study drug is not deniable (1. definitely related, 2. probably related, 3. possibly related), the event is considered as an adverse reaction.

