- 1. Handling of personal data

For enrollment of a subject and preparation of his case report form, the investigator, etc. identify him by the subject identification code to retain the information as linkable anonymized data. Thus, personal data of a subject must be handled with caution.

1. Storage and destruction of records
   1. Storage of records

The investigator, etc. retains following records and documents for 5 years: case report forms, laboratory data, documents of ethical committee, documents on subject’s consent, documents on treatment with study drug and the study-related data.

- 1. Destruction of records

After completion of the storage period of records, the study-related data will be destroyed adequately, not to leak such secrets as personal data of subjects.

1. Statistical analysis

In this study, statistical analysis will be performed mainly for the following items. Details of the statistical design will be described in the statistical analysis plan.

- 1. Demographic characteristics

In addition to summary of subjects, summary statistics of demographic variables (including gender and age) of subjects will be shown.

- 1. Analysis set

Analysis set of the study will be Full analysis set (FAS) consisting of all subjects enrolled in the study, except for those described below.

• Subjects who were found to be ineligible for the study after the registration

• Subjects who took no study drug

• Subjects who had no efficacy data

- 1. Analysis methods for efficacy endpoints
     - 1. Primary endpoint

The summary statistics will be calculated for the permeability of the small intestine at baseline and after treatment respectively (mean, median).

For the primary analysis, (permeability of the small intestine after treatment - permeability of the small intestine at baseline) will be sought for each subject and the corresponding Wilcoxon test will be performed. The significance level will be 5% on both sides. For reference, the 2 groups will be compared using the Analysis of Covariance with permeability of the small intestine at baseline as a covariate.

- - - 1. Secondary endpoint

For endotoxin activities in blood and changes in the intestinal flora, too, (values after treatment - values at baseline) will be sought for each subject and the paired Wilcoxon test will be performed. The significance level will be 5% on both sides. For reference, the 2 groups will be compared using the Analysis of Covariance with baseline value as a covariate.

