- 1. Analysis methods for safety endpoints

The type, severity, and incidence of adverse events and adverse reactions that occurred will be calculated and compared between the 2 groups.

- 1. Design of sample size

This study will be conducted for healthy volunteers as pilot positioning. Because the prior data do not exist, the scheduled number of registered subjects will be 30 subjects who are considered to be collectable within the specified study period.

1. Financing source and conflict of interest associated with the study

The study is sponsored by Abbott Japan Co., Ltd. and will be conducted by Yokohama City University as a contract research by Abbott Japan Co., Ltd.

Responsible person for study will declare any conflict of interest according to conflict of interest management rules of the study site.

The investigator will prepare the database to be used in this study by making it anonymous and Abbott Japan Co., Ltd. can neither access it nor perform statistical analysis using the database. Evaluation and interpretation of the results of the study will be performed by the investigator. The results of the study will not be disclosed unless the written consent is obtained according to the confidentiality rules.

1. Expenses on study participation

A research cooperation expenditure will be 50,000 yen per subject.

The investigator will purchase diclofenac sodium and study drug which will be used in the study.

1. Publication of the results

Whatever the study results may be, the principal investigator will publish the results in a scientific journal or in a scientific meeting.

Until 60 days prior to the publication of the study results, the investigator or the study site will submit the manuscript with the same contents to Abbott Japan Co., Ltd. to request their review and comments.

1. Study organization
   1. Responsible person for study (Investigator)

Department of Gastroenterology and Hepatology Yokohama City University Hospital
Professor   [name]

- 1. Sub-investigator

Department of Gastroenterology and Hepatology Yokohama City University Hospital
Postgraduate     [name]

Department of Gastroenterology and Hepatology Yokohama City University Hospital
Medical advisor   [name]

Department of Gastroenterology and Hepatology Yokohama City University Hospital
Postgraduate    [name]

Department of Biostatistics, Yokohama City University Graduate School of Medicine
Professor   [name]

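### The adverse-reaction endpoint rests on two conflicting causality rules, and the between-group safety comparison is not limited to events after allocation

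*Protocol*

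**What the plan says.** Section numbers below are counted from the order of the protocol's headings.

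- **Causality (11.4).** There are two categories. Related: "Temporal relationship is observed clearly and causes other than study drug can be excluded". Unrelated: "No temporal relationship is observed or the event can be explained by other causes".
- **Definitions of adverse reactions (11.6).** The test is different: "When causal relationship between an adverse event and study drug is not deniable (1. definitely related, 2. probably related, 3. possibly related"), and any such event is an adverse reaction.
- **Meaning of *study drug*.** The Background reserves the term for lubiprostone. The Study drugs section lists Voltaren and Amitiza together, and the section on expected adverse reactions applies the term to the Interview Forms of both.
- **Where the definition is used.** The safety endpoints are "Adverse events, adverse reactions". The Study termination criteria discontinue a subject who has an adverse reaction of Grade 2 or higher.
- **Collection and allocation.** Section 11.1 states that "adverse events will be collected during the period from the start of treatment with diclofenac sodium to the end of treatment with study drug". Allocation comes later: "After administering diclofenac sodium for 7 days, the investigator, etc. will perform medical examination and allocate the subjects who can move to the study period".
- **Analysis (22.4).** "The type, severity, and incidence of adverse events and adverse reactions that occurred will be calculated and compared between the 2 groups". The Statistical analysis section adds: "Details of the statistical design will be described in the statistical analysis plan".

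**The concern.** Sections 11.4 and 11.6 give different answers for the events that matter most here. All subjects have just finished a week of diclofenac, and the main expected reactions to both drugs are gastrointestinal. For a gastrointestinal complaint early in the lubiprostone period, a competing explanation is therefore built into the design. Whether that complaint is an adverse reaction depends on which paragraph the investigator follows. Two investigators could report different endpoint counts from the same events and apply the discontinuation criterion differently.

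The analysis plan cannot fully repair this. Causality is recorded on the case report form. If the form follows 11.4, a two-level answer cannot later be split into definite, probable and possible.

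There are two related weaknesses. First, it is unclear which drug causality is judged against. If it is lubiprostone alone, controls are never exposed, and comparing adverse reactions between arms tells nothing. If it is both drugs, diclofenac reactions enter a comparison meant to isolate lubiprostone. Second, the safety comparison sets no lower time limit, so as worded it takes in events from before allocation.

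**Working it through.** **1. The two rules side by side, for an event during the lubiprostone period**

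| Situation | Section 11.4 | Section 11.6 |
| --- | --- | --- |
| Clear timing, other causes excluded | Related | Adverse reaction |
| Clear timing, diclofenac could also explain it, lubiprostone cannot be denied | Unrelated | Adverse reaction (possibly related) |
| No temporal relationship | Unrelated | Not an adverse reaction, if causality is thereby denied |

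The middle row is the contradiction. The grades in 11.6 do not exist in 11.4, so one scale cannot be mapped onto the other.

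**2. Rates quoted in the protocol (Expected adverse reactions of study drug)**

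- Lubiprostone, 48 µg/day: 196/315 = 62.2%
- Diclofenac, up to approval: 160/1,474 = 10.85%
- Diclofenac, post-marketing: 2,749/35,653 = 7.71%

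All three reproduce. The protocol gives no design figure for safety (no test, power or significance level), so there is none to reproduce.

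**3. How far the two definitions could differ**

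The Design of sample size section gives 30 subjects and the Target sample size section gives 35, so about 15 or 17 per arm. Let s be the share of broad-definition reactors who fail the exclusion test in 11.4. The documents do not give s; 25% to 75% is assumed. The 62% is taken to correspond to the broad definition, which is also an assumption.

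- Broad count = n × 0.62: 15 × 0.62 = 9.3; 17 × 0.62 = 10.5
- Strict count = n × 0.62 × (1 − s):

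| s (assumed) | n = 15 | n = 17 |
| --- | --- | --- |
| 25% | 7.0 | 7.9 |
| 50% | 4.7 | 5.3 |
| 75% | 2.3 | 2.6 |

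**4. Diclofenac-week events**

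Expected subjects with a diclofenac reaction:

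- 30 × 0.0771 = 2.3 and 30 × 0.1085 = 3.3
- 35 × 0.0771 = 2.7 and 35 × 0.1085 = 3.8

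So about 2 to 4 subjects, before removing any who are not allocated.

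With a run-in rate r that is the same in both arms and independent of later events, the rate over the whole window is 1 − (1 − p)(1 − r). The difference between arms is therefore multiplied by (1 − r). As an illustration, take post-allocation rates of 62% (treated) and 10% (control, assumed):

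- Post-allocation only: 62 − 10 = 52 points
- r = 10.85%: 66.1% against 19.8%; 52 × 0.8915 = 46.4 points
- r = 5%: 52 × 0.95 = 49.4 points
- r = 30%: 52 × 0.70 = 36.4 points

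If the post-allocation rates are equal, the difference stays zero. The effect is dilution, not bias.

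**The case against.** The defence has good points, and most of them limit the concern.

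- **The safety comparison as a whole is not invalid.** A reader might infer that it is, but Section 22.4 also compares adverse events as such, and that comparison uses no causality judgement.
- **Run-in events do not favour either arm.** Allocation follows the diclofenac week, so they are balanced in expectation.
- **The protocol does not say in terms that run-in events are counted.** Onset dates are recorded, so periods can be separated, and a rule for events arising after allocation could sit in an analysis plan that is not shown. What stands is narrower: the protocol's own sentence carries no such limit.
- **The collection window is not open-ended for controls.** It might look so, because they receive no lubiprostone. But the protocol uses the study-drug treatment period as a label for both arms: the Physical findings item lists adverse events for both groups in that period, and the control group has a matching 14- or 28-day period ending in an examination.
- **The strict count need not be close to zero.** The documents give no share of events that diclofenac could explain. Diclofenac lasts 7 days and the period after it 14 or 28, so later events are less readily put down to it.
- **The 62% transfers poorly.** It comes from 48 µg/day and includes abnormal laboratory findings. This trial gives one 24 µg capsule daily and assesses events on clinical symptoms.
- **The 2 to 4 run-in cases are only a guide.** Subjects who cannot move to the study period are never allocated and so drop out of a two-group table, and the quoted rates are not specific to 7 days.

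None of this resolves the conflict between 11.4 and 11.6.

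**Conclusion.** The adverse-reaction endpoint is contradictory as written, and this should be corrected. The same event can be Unrelated under one paragraph and an adverse reaction under the next, and it is unclear against which drug the judgement is made. The consequences reach the endpoint, its between-group comparison and the Grade 2 or higher discontinuation criterion. They do not reach the plain adverse-event comparison.

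The size cannot be fixed from the documents. On the assumed range, 9.3 of 15 treated subjects under the broad rule become 7.0 to 2.3 under the strict one. The true figures are probably lower, because the 62% is probably high for this trial.

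The missing limit to post-allocation events is a secondary point. On the illustrative rates it shrinks a 52-point difference to 46.4 points at a 10.85% run-in rate. The documents support loss of contrast, not a biased or invalid comparison.

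**What to change.** - Reconcile Sections 11.4 and 11.6 into one causality scale and one rule for what counts as an adverse reaction, with the case report form collecting every grade that the rule needs. Which definition governs is for the investigators to decide, because it feeds the discontinuation criterion.
- Reconcile that criterion with the agreed rule. It also cites Section 11.6 for moderate and severe, whereas by heading order severity is in 11.5.
- Name the drug to which causality is judged, and record causality separately for diclofenac and lubiprostone.
- In Section 22.4, limit the between-group comparison to adverse events with onset or worsening after allocation. Tabulate diclofenac-week events separately, and report lubiprostone adverse reactions descriptively for the lubiprostone arm.

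The cost is wording in these sections, one extra field on the case report form and slightly more tabulation. No visit is added.
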